### Recruitment

Pharmacies, pharmacists, and patients will be recruited in the province of Québec. Pharmacists will first be invited to participate in the study through advertisements such as those on the social media platforms of the provincial pharmacy college, the *Ordre des pharmaciens du Québec* (OPQ) and Facebook groups for pharmacists. The research team will also reach out directly via phone, email, or in person. Interested pharmacists will be provided with study details, and pharmacy eligibility will be verified. Eligibility will be determined by confirming that at least one patient has initiated an AET in the last 30 months as a client in the pharmacy (verified by the pharmacists). If that is the case, interested pharmacists will be asked to invite other pharmacists in their pharmacy to participate, identify a pharmacist responsible for overseeing the study in their pharmacy, and inform the pharmacy owner of their intent to participate. In each pharmacy, a member of the pharmacy team will contact potentially eligible patients to provide a brief overview of the study and request their permission to be contacted by a research team member for further details. A research team member will verify eligibility criteria with each patient. If the patient is eligible and agrees to participate, a link to the consent form and baseline questionnaire will be sent. A consent form and a baseline questionnaire will also be sent to pharmacists agreeing to participate.

Participants for the qualitative part of the study will be selected at the end of the follow-up to reflect on different characteristics likely to influence the experience with AET and/or with the program (for example, for the patient: age, type of AET, time since AET initiation, satisfaction with the program or AET services received in pharmacy; for the pharmacists: sex, years of experience, use of the program components, and/or AET services dispensed). This selection will be performed based on the information from the questionnaires.

### Allocation and blinding

When all the consent forms and baseline questionnaires are completed, the pharmacy, its pharmacists and patients form a cluster and will be randomized (see Fig. 2). Each cluster will be randomly assigned to the PACHA program or the UC group using a 1:1 allocation ratio. A biostatistician, external to the study team, generated the randomization sequence using variable block sizes and prepared numbered, sealed envelopes to be opened in a strict order. After randomization, no other pharmacist or patient can be added to the cluster. Program components are available exclusively to pharmacies randomized to the PACHA program group. Pharmacists and patients are not blinded to the intervention, but data analyses will be conducted in a blinded fashion.

**Fig. 2 Fig2:**
[figure not shown]
CONSORT diagram illustrating participants’ flow throughout this pilot cluster RCT

### Outcomes

The assessment plan for the study outcomes is presented in Table 3. *Program acceptability* will be assessed through participation and retention rates, uptake of program components, satisfaction, and participants’ perspectives on the relevance, acceptability, and perceived benefits of each program component. *Feasibility of the implementation of the PACHA program* will be evaluated using indicators based on the Framework for the Implementation of Services in Pharmacy [26], which includes indicators related to the implementation process, implementation impact, and implementation outcomes. The *implementation process* will be evaluated through the extent of program delivery (e.g., limited to some program components or its full capacity). The *implementation impact* will be assessed through factors and strategies influencing implementation at individual and environmental levels. *Implementation outcomes* will take into account reach and fidelity. Reach and fidelity indicators will include the timing of program components' uptake and delivery. Also, the dynamics of implementing the PACHA program in community pharmacies will be assessed with the noMAD questionnaire [47, 48] derived from the Normalization Process Theory of the implementation of complex health interventions [49].

**Table 3 Tab3:** Assessment plan for the study outcomes

Outcome	Mode of measurement	Analysis of metric	Timeline			Group of participants assessed	
			Baseline	Throughout	End of study	Pharmacists	Patients
**Acceptability**							
Participation and retention rate	- Study data log	- Descriptive statistics		X	X	X	X
Uptake of program components	- Questionnaire - Website metrics	- Descriptive statistics		X	X	X	X
Satisfaction	- Questionnaire - Semi-structured interview	- Descriptive statistics - Thematic analysis			X	X	X
Perceived relevance, acceptability, and benefits	- Semi-structured interview	- Thematic analysis			X	X	X
**Feasibility of implementation**							
Extent of program delivery	- Questionnaire - Semi-structured interview - Website metrics	- Descriptive statistics - Thematic analysis		X	X	X	
Factors and strategies influencing implementation	- Semi-structured interview	- Thematic analysis			X	X	
Reach and fidelity: timing of program component uptake and delivery	- Questionnaire - Semi-structured interview - Website metrics	- Descriptive statistics - Thematic analysis		X	X	X	X
Dynamics of implementing complex interventions	- Questionnaire	- Descriptive statistics			X	X	
**Preliminary effects on factors expected to influence adjuvant endocrine therapy adherence**							
Intention to adhere to adjuvant endocrine therapy	- Questionnaire	- Mean change	X		X		X
Adjuvant endocrine therapy knowledge	- Questionnaire	- Mean change	X		X		X
Attitude towards adjuvant endocrine therapy	- Questionnaire	- Mean change	X		X		X
Perceived social support	- Questionnaire	- Mean change	X		X		X
Perceived behavioral control	- Questionnaire	- Mean change	X		X		X
Anticipated regret	- Questionnaire	- Mean change	X		X		X
Coping planning	- Questionnaire	- Mean change	X		X		X
Fear of recurrence	- Questionnaire	- Mean change	X		X		X
Side effects	- Questionnaire	- Mean change	X		X		X
Cognitive representations of the medication	- Questionnaire	- Mean change	X		X		X
Patient-provider relationship	- Questionnaire	- Mean score			X	X	X
Quality of life	- Questionnaire	- Mean change	X		X		
Adherence	- Questionnaire - Pharmacy claim records	- Descriptive statistics			X		X
**Feasibility of a large-scale cluster randomized controlled trial**							
Recruitment rates and channels	- Recruitment algorithm	- Descriptive statistics		X	X	X	X
Reasons for refusal	- Study data logs	- Descriptive statistics		X		X	X
Randomization process	- Recruitment algorithm	- Descriptive statistics		X		X	X
Cluster size	- Study data logs	- Descriptive statistics		X			
Frequency of contact between participants and research team	- Study data logs	- Descriptive statistics		X		X	X

Outcomes related to the *preliminary effects on factors expected to influence AET adherence*, such as intention to adhere to AET, AET knowledge, attitude, perceived social support, behavioral control, anticipated regret, and coping planning, will be assessed by questionnaire. We developed this questionnaire following the recommendations of the developers of the Theory of Planned Behavior [50] and our previous qualitative study [32]. The questionnaire was validated in a test–retest study among 67 patients with an AET, and each scale presented very good psychometric properties (Cronbach’s alphas and intraclass correlation coefficients ≥ 0.70). Other important measures will be collected using validated measures in their official French versions: side effects (Functional Assessment of Cancer Therapy—Endocrine Symptoms (FACT-ES) [51]), fear of cancer recurrence (Fear of Cancer Recurrence Inventory [52]), beliefs about medication (Beliefs about Medicine Questionnaire – adjuvant endocrine therapy [53]), patient-pharmacist relationship (Consultation and Relational Empathy (CARE) measure [54, 55]), and quality of life (Functional Assessment of Cancer Therapy – Breast (FACT-B) [56]).

We will appraise the program's preliminary effects on *AET **adherence* (AET initiation, implementation, and persistence) [57] through self-reported measures (i.e., using questions developed by our team and the Medication Adherence Report Scale (MARS) [58]) and calculate it using pharmacy claims for the 6-month follow-up. Data on drug identifier, delivery date, prescribed regimen, and duration of supply will be used to calculate AET initiation, non-persistence, and implementation for any AET, not just the one initially prescribed. Non-persistence will be defined as not claiming an AET at the expected date, allowing for a 90-day permissible gap. Implementation will be defined through the proportion of days covered (PDC) by any AET divided by the number of days of follow-up [59].

Information on the *feasibility of a large-scale cluster RCT* will be gathered through recruitment rates (% of eligible and enrolled pharmacists and patients, time for recruitment), recruitment channels, reasons for refusal, randomization process, cluster size, and frequency of contact with the research team. *Characteristics* of pharmacies (e.g., number of daily prescriptions delivered) and pharmacists (e.g., years of experience), as well as sociodemographic and medical characteristics of the patients (e.g., age, other breast cancer treatment received) will be collected in the baseline questionnaire. *Co-interventions* (i.e., other services received regarding AET) will be collected in the 6-month questionnaire completed by patients. *Costs* of program development and delivery will be documented by the research team.

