## Methods

### Study design and setting

This is a pilot cluster-RCT with a 6-month follow-up, using mixed methods (quantitative and qualitative) and recruiting in the province of Québec, Canada. Following the Medical Research Council framework for complex interventions [25], the PACHA program and study procedures will be pilot-tested to guide decisions regarding the development of a large-scale, cluster-RCT assessing the effects of the program on 5-year AET adherence and healthcare system costs. The need for a pilot study lies in the novelty of the program and the anticipated challenges related to implementing interventions and conducting a RCT in community pharmacies [26]. A cluster is defined as a community pharmacy, its pharmacists, and its recruited patients. Cluster randomization is necessary to prevent between-group contamination (i.e., pharmacists in the control group exposed to PACHA training and tools). The PACHA program will be compared to usual community pharmacy practice. Each cluster will be followed for 6 months after their inclusion in the study (randomization). See Table 1 for the study timetable. This trial has been approved by the Research Ethics Board of the CHU de Québec-Université Laval (MP-20–2023-6625) and registered at Clinicaltrials.gov (NCT05887102) on 2023–05–24, prior to beginning the study. The study is presented according to the SPIRIT recommendations [27].

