### Eligibility criteria

*Community pharmacies* are eligible to participate if (1) at least one pharmacist agrees to take charge of the project in their pharmacy and provides consent; and (2) at least one patient has initiated AET in the last 30 months in the pharmacy and provides consent. *Patients* are eligible if they (1) are a woman; (2) ≥ 18 years; (3) were diagnosed with a first non-metastatic, hormone-sensitive breast cancer (endocrine therapy may also be prescribed to patients with metastatic disease, but in this case, the patient takes the drug to treat active cancer and so, adherence issues may differ); (4) received an AET prescription for the first time in the last 30 months; (5) are fluent in French (78% of the Quebec population) [46]; (6) have internet access; and (7) provide consent. Excluded are patients who live in a residential facility where AET is not self-managed.

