### Sample size

We estimated that most clusters would include between 1 and 3 patients (mean = 2) and that we would be able to recruit approximately 33 pharmacies and 66 patients per group. To assess the precision of our acceptability and feasibility indicators, we calculated Wald 95% confidence intervals (CI) [62] taking into account an intra-cluster correlation (ICC) of 0.02 for patients from the same pharmacy [63]. For example, for the acceptability indicator defined by a participation rate of at least 50% of eligible patients, a sample size of 132 patients will lead to a 95% CI of 41.5% to 58.5%. For one of our main feasibility indicators, which is at least 70% of pharmacists completing the training, a sample size of 33 pharmacists will result in a 95% CI of 54.4% to 85.6%. Finally, for the indicator assessing whether at least 75% of pharmacists and patients deem the program acceptable and potentially beneficial, a sample size of 33 pharmacists and 66 patients will result in a 95% CI of 60.2% to 89.8% and 64.4% to 85.6%, respectively. This pilot study is not designed to assess the program’s efficacy on adherence [64]. However, we will be able to explore the program’s preliminary effects on factors expected to influence AET adherence. The anticipated sample size will enable us to detect moderate to large effect sizes (*d* ≥ 0.50) (mean of 2 patients per cluster; ICC = 0.02 [63]; correlation of 0.5 between baseline and 6-month follow-up [65]; power = 0.80; α = 0.05). For the qualitative phase, we will determine the final number of semi-structured interviews to be conducted for each group (pharmacists and patients) using data saturation (i.e., when no new information is provided by the interviews). From our previous work conducted among these groups [66–68], saturation may be reached after 15 to 20 interviews.

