### Analyses

Descriptive statistics for pharmacies, pharmacists, and patients in the PACHA program and UC group will be reported and compared. Acceptability and feasibility indicators such as recruitment and retention rates will be evaluated using percentages or means and 95% CI [69]. To explore preliminary effects on factors expected to influence AET adherence, generalized estimating equation (GEE) regression models will be used to compare patterns of change in scores of factors influencing AET adherence between the two groups over time. The group-by-time interaction *p*-value will be used to test the differences between the two groups. Effect sizes will be estimated using Cohen’s *d*. The required sample size for a large-scale cluster RCT will be estimated using the PDC, its variability, and ICC. Missing data will be handled using various strategies according to the variables. For instance, mean score imputation (if at least half of the items are completed) will be applied to scales, while listwise deletion will be used for other variables [70]. For qualitative data, thematic analysis of the interviews will be conducted [71, 72]. Since this is a pilot study, analyses will be performed at the end of the study, and no subgroup analyses will be performed.

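### Claims-based non-persistence needs a 90-day gap inside a 6-month window, so supply that ends after about day 90 to 94 is always classified as persistent

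*Protocol article*

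**What the plan says.** The Outcomes section of the protocol article, in the paragraph on AET adherence after Table 3, names three components of adherence: "AET initiation, implementation, and persistence". They are self-reported, and the team will also "calculate it using pharmacy claims for the 6-month follow-up". The persistence rule is "Non-persistence will be defined as not claiming an AET at the expected date, allowing for a 90-day permissible gap". PDC is taken over the days of follow-up. Under Study design and setting, the six months run from randomization.

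Other sections limit the role of this measure:

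- Table 3 gives adherence descriptive statistics only, at end of study.
- Sample size states "This pilot study is not designed to assess the program’s efficacy on adherence".
- Progression criteria contain no persistence or adherence item.
- Analyses states "The required sample size for a large-scale cluster RCT will be estimated using the PDC, its variability, and ICC".

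The article mentions no claims beyond month 6, no shorter gap, and no rule for a gap still open when follow-up ends.

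**The concern.** The permissible gap is about half as long as the observation window. A woman becomes non-persistent only after 90 days without a refill, counted from the date the refill was due, and those 90 days must fit before month 6. If her supply ends in the second half of follow-up, the rule cannot return the event whatever she does, and she is counted as persistent.

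Three things follow for the claims-based measure:

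- The reported 6-month proportion leaves out a large share of the discontinuations it is meant to describe.
- The two claims measures disagree. The same uncovered days that persistence ignores lower the PDC, so a stop appears as poor implementation.
- Table 2 schedules the second consultation at 4 months, about day 120, after the last supply-end date that can yield an event. A discontinuation after that contact, or one prevented by it, cannot show in this measure.

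**Working it through.** The article gives no rate, power or sample size for non-persistence, so there is no stated figure to reproduce. The check is direct arithmetic.

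**Inputs from the article.** Gap 90 days and claims for six months (Outcomes). Start at randomization (Study design and setting). 66 patients per group (Sample size). Five-year non-persistence of 31% and 47% (Background).

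**Assumptions, not from the article.** Six months is 180 to 184 days (183 where one value is needed). Supplies last 30, 60 or 90 days. Other assumptions are stated at each step.

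**1. Last supply-end day that can give an event** = window − 90.
- 180 − 90 = day 90; 184 − 90 = day 94.
- Share of the window in which a supply end cannot give an event: 90/180 = 50.0%; 90/184 = 48.9%.

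If supply-end dates are uniform over follow-up, about half of discontinuations are missed.

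**2. Last fill that can give an event** = window − 90 − days supplied.

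| Supply | Last qualifying fill |
|---|---|
| 30 days | day 60 to 64 |
| 60 days | day 30 to 34 |
| 90 days | day 0 to 4 |

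**3. Effect of supply in hand.** Let the stopping day be uniform over 183 days and the supply left at that moment uniform between 0 and s days, so on average s/2. Then
- classified as non-persistent: (183 − 90 − s/2)/183
- supply ends inside the window but the gap cannot complete: 90/183
- supply outlasts month 6: (s/2)/183

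| s | Classified | Gap cannot complete | Supply outlasts month 6 |
|---|---|---|---|
| 30 | 78/183 = 42.6% | 49.2% | 8.2% |
| 60 | 63/183 = 34.4% | 49.2% | 16.4% |
| 90 | 48/183 = 26.2% | 49.2% | 24.6% |

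A simulation under the same assumptions gave 42.7%, 34.3% and 26.2%. So 57% to 74% of stops are missed. The 49.2% is due to the gap rule. The last column would escape any rule confined to six months of claims.

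**4. Disagreement with PDC.** A woman fully covered to just past day 93 who never refills has a PDC of about 93/183 = 0.51 and is persistent.

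**5. Scale in women.** Assume a constant hazard, and take stopping and supply end as the same day.
- 31%: hazard = −ln(0.69)/5 = 0.0742 per year. Risk 3.64% at 6 months and 1.84% at 3 months. Times 66: 2.4 stop, 1.2 are detectable.
- 47%: hazard = −ln(0.53)/5 = 0.1270 per year. Risk 6.15% and 3.12%. Times 66: 4.1 stop, 2.1 are detectable.

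About 1 to 2 women per group are missed, and somewhat more once supply in hand is allowed for as in step 3.

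**The case against.** The strongest reply is that nothing in the pilot depends on this measure. That stands, and it limits the weight of the point. A reader might infer that a wrong persistence estimate would be carried into planning the 5-year trial. The documents do not support that: the later trial is to be sized on PDC, which does register the uncovered days, and no section carries a persistence figure forward.

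A reader might also infer that late discontinuations are invisible to the study. They are not. Self-report at end of study (MARS and the team's own questions) can record them, and PDC falls.

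A third tempting reading joins two claims: that the rate is biased towards zero overall, and that women who stopped before randomization would be counted as events. Eligibility asks only that a woman "received an AET prescription for the first time in the last 30 months", so earlier stoppers can enrol. But the article does not say how they would be classified, and if they were counted the error would run the other way. The net direction is therefore not established.

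Finally, a condensed article may leave the extraction date to the full protocol. It may, and claims collected for at least 90 days past month 6 would remove the problem. But the article states both the period of the claims and the gap. Applied as written, the two return the wrong class for late stops, which is more than a missing detail.

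**Conclusion.** The point holds for the claims-based non-persistence measure and no further. As written, the rule cannot classify a woman as non-persistent if her supply ends after about day 90 to 94. That part rests only on the article's own 90-day gap and six-month window. The size of the loss rests on assumptions: about half of discontinuations if supply-end dates are uniform, and 57% to 74% if stopping dates are uniform and supplies last 30 to 90 days. In absolute terms this is a handful of women at most in a pilot of this size.

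The resulting proportion should not be read as 6-month non-persistence, and it has little sensitivity to a group difference arising late in follow-up. Because the measure is descriptive and exploratory, this is a minor to moderate point.

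**What to change.** Within the six-month window:

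1. Apply the 90-day definition only to refills due by about day 90, and label the result as discontinuation beginning in the first half of follow-up.
2. Add a shorter-gap definition, for example 30 or 45 days, and treat gaps still open at month 6 as censored, not persistent. Under the assumptions of step 3 above, the share of stops classified would be (183 − 30 − s/2)/183 = 75%, 67% and 59% for a 30-day gap, and (183 − 45 − s/2)/183 = 67%, 59% and 51% for a 45-day gap, at supplies of 30, 60 and 90 days.
3. Count as at risk only women with AET supply at randomization, and report the others separately.

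This uses records already being obtained and needs only a revised definition before claims are analysed. The price of a shorter gap is that some late refills will be labelled as discontinuation, so both definitions should be shown.

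Optionally, if consent allows, extract claims to about day 270 (180 + 90) and classify gaps beginning by day 180. That delays results by about three months. Table 2 also offers usual-care pharmacists the training, and gives usual-care patients the website, at the end of the study, so refills after month 6 in that group may follow access to the program.

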### Data collection and management

Quantitative outcomes will be collected through the Research Electronic Data Capture (REDCap) online platform [60]. Pharmacists and participating patients will be asked to complete two online questionnaires: one before randomization and another at the end of the 6-month follow-up. Non-responders will be reminded using email and telephone. Qualitative data will be collected at the end of the study through semi-structured interviews. These interviews will be conducted by telephone or Teams and audio-recorded. Participants’ confidential information will be managed according to best practices, stored on a secured server, and kept in password-protected documents accessible only to a limited number of research team members who have signed a confidentiality agreement.

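### No baseline adherence is scheduled and PDC is tied to the 6-month follow-up, in women up to 30 months into AET, which weakens the pilot's PDC inputs for sizing the full trial

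*Protocol article*

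**What the plan says.** The Outcomes section says the team will collect self-reported adherence (its own questions and MARS) and "calculate it using pharmacy claims for the 6-month follow-up". Under Study design and setting, each cluster's 6 months run from randomization. For the claims measure, "Implementation will be defined through the proportion of days covered (PDC) by any AET divided by the number of days of follow-up".

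Women qualify if they "received an AET prescription for the first time in the last 30 months" (Eligibility criteria), so time on treatment at entry can be anything from 0 to 30 months.

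In Table 3 the Adherence row gives the mode as "Questionnaire - Pharmacy claim records" and the analysis as descriptive statistics, with a timing mark under end of study only. Of the 13 rows in that block, 11 carry a baseline mark. The only other row without one is the patient-provider relationship. Participants already complete two questionnaires, "one before randomization and another at the end of the 6-month follow-up" (Data collection and management).

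The Analyses section sizes the full-scale trial from PDC, its variability and its ICC. The Sample size section states that the pilot is not designed to test efficacy on adherence, while Outcomes says preliminary effects on adherence will be appraised.

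**The concern.** Many women will probably be mid-treatment at randomization, with an adherence history and tablets left from an earlier fill. Two things follow.

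- **No prior adherence.** Past adherence is likely to be a strong predictor of later adherence. Without it, an arm comparison of 6-month PDC cannot be adjusted for it, and the pilot cannot report the correlation that would tell the full trial how much adjustment saves.
- **Supply in hand.** A strict reading of the claims window would use only fills dated after randomization. The days before a woman's first such fill would then score as uncovered even though she holds tablets. PDC would fall, and its spread would grow with fill length.

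Both bear on the one design use the protocol gives to PDC, which is sizing the next trial.

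**Working it through.** **The plan's own figure.** The only power statement concerns the psychosocial scores: d ≥ 0.50 with 66 women per group, mean cluster size 2, ICC 0.02, correlation 0.5, power 0.80, α 0.05 (two-sided assumed).
- SD of change = √(2(1 − 0.5)) = 1.
- n = 2(1.960 + 0.842)²/0.5² = 62.8, so 63 per group.
- Design effect = 1 + (2 − 1)(0.02) = 1.02, and 63 × 1.02 = 64.3, within 66. Power at 66 is 0.81.

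The figure reproduces, and this point does not change it. No such figure is given for PDC.

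**Value of a baseline measure.** With covariate adjustment the required number is multiplied by 1 − r², where r is the correlation of baseline with 6-month PDC. The protocol's 0.5 is for the psychosocial scores, so r for PDC is an assumption:
- r = 0.3: 1 − 0.09 = 0.91
- r = 0.5: 1 − 0.25 = 0.75
- r = 0.7: 1 − 0.49 = 0.51

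**Supply in hand, if it were ignored.** Inputs: a window W of 182 days; fill length L of 30, 60 or 90 days (assumed); a perfectly adherent woman; and R days of supply left at randomization, equally likely to be 0 to L − 1 (assumed). Then PDC = (W − R)/W, with mean 1 − (L − 1)/(2W) and SD √((L² − 1)/12)/W. PDC is below 0.80 when R is 37 or more.

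| Fill length | Mean PDC | SD | Share below 0.80 |
|---|---|---|---|
| 30 days | 1 − 14.5/182 = 0.920 | 8.66/182 = 0.048 | 0% |
| 60 days | 1 − 29.5/182 = 0.838 | 17.32/182 = 0.095 | 23/60 = 38% |
| 90 days | 1 − 44.5/182 = 0.755 | 25.98/182 = 0.143 | 53/90 = 59% |

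A 180-day window with R continuous on 0 to L gives nearly the same: 0.917 (SD 0.048) for 30 days and 0.750 (SD 0.144) for 90 days. With supply carried in, every one of these women has a PDC of 1.00.

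**Effect on sizing, if it were ignored.** Assume a true PDC SD of 20 points and an independent artefact. Sample size scales with variance:
- 30-day fills: √(20² + 4.8²) = 20.6, factor 1.06
- 60-day fills: √(20² + 9.5²) = 22.1, factor 1.23
- 90-day fills: √(20² + 14.3²) = 24.6, factor 1.51

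For a true SD from 15 to 25 points the factors run from 1.10 down to 1.04, 1.40 down to 1.14, and 1.91 down to 1.33.

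**The case against.** A reader might infer that the plan counts supply in hand as uncovered days. The text does not say so. A day covered by a fill made before randomization is still covered, and the 6-month phrase can describe the period over which adherence is calculated rather than a cut-off on dispensing dates. The article even points the other way: "Data on drug identifier, delivery date, prescribed regimen, and duration of supply will be used to calculate AET initiation, non-persistence, and implementation". Non-persistence is judged against the expected date of the next claim, which for a first refill after randomization can come only from an earlier fill. The carry-in rule is also a detail that an article may leave to the full protocol or SAP. This part of the objection stands, so the artefact is a conditional risk and not a stated feature.

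A reader might also infer a biased arm comparison. Any carry-in loss should be similar in two randomized arms, so it would mainly distort the level and spread of PDC. Randomization makes the contrast valid without a baseline covariate; what is lost is precision. In addition, adherence is only described in Table 3, no progression criterion uses it, and an inflated variance would make the next trial larger rather than underpowered. All of this stands and lowers the severity.

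Finally, Table 3's end-of-study mark may only record when claims are extracted, and earlier claims could be retrieved later. That is fair for claims, though nothing in the article calls for a look-back. It does not answer the point on self-report: MARS not asked before randomization cannot be recovered.

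**Conclusion.** The point holds in a limited form and is moderate. Following the article as written gives no baseline adherence by either method, in a cohort whose treatment history may reach 30 months, and no baseline-to-follow-up correlation for a full trial that will be sized from PDC. The saving forgone is a factor of 0.91 to 0.51 in sample size for r between 0.3 and 0.7, with r assumed.

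The loss from ignoring supply in hand applies only if fills before randomization were left out. It would be small with 30-day fills and substantial with 90-day fills. It rests on assumed fill lengths, evenly spread residual supply and an assumed true SD, none of which the document gives. It does not support a claim that PDC is wrongly defined, that the arms would be compared unfairly, or that prior adherence is beyond recovery from claims.

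**What to change.** - Extend the claims extraction to at least 6 months before randomization, or to AET initiation if that is later.
- State that supply in hand at randomization is carried into follow-up days.
- Compute baseline PDC from the look-back and use it as a covariate in any arm comparison of 6-month PDC. Say how women with little or no look-back, because they have only just started, will be handled.
- Report the baseline-to-follow-up correlation and the adjusted variance of PDC, alongside the ICC, as inputs for sizing the full trial.
- Add MARS to the existing pre-randomization questionnaire and mark it at baseline in Table 3. This can help only women not yet randomized.

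The cost is a wider date range on the same extraction, one short scale, and matching protocol and consent wording. No extra visits are needed.
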